## 16. TREATMENT OF SUBJECTS

### 16.1 Investigational treatment

The treatment, or intervention, in our study is best described as withholding PN in the early course of disease to reach currently recommended energy and protein intakes, when enteral delivery of these intakes is insufficient. In both allocation groups of the study, patients will be evaluated on a day to day basis to see which amount of enteral intake can be provided. The “early PN” group will receive current standard nutritional practice, which prescribes that PN should be added to EN as soon as possible in the course of disease, to achieve energy and protein goals. In the “late PN” group, we will wait to add PN, when EN is insufficient, until day 7.

[figure not shown]

“Late PN”, the so-called “intervention-group”.

In Leuven, Rotterdam and Edmonton patients randomised to the “late PN” group will receive a mixture of Glucose 5% and NaCl 0.9% at, respectively, 60% and 40% of the total flow rate that is required to obtain standard optimal hydration taking into account the volume of EN that is being delivered. If enteral feeding of at least 80% of the calculated calories is not possible after 7 days in ICU, PN, as specified below, is initiated on day 8.

The infusions will be supplemented with micronutrients and vitamins as they would have received when provided PN.

When the blood glucose levels fall spontaneously below 50 mg/dl, the standard glucose of 5% in the late PN group will be switched to 10% glucose until blood glucose level is above 80 mg/dl. At this point the infusion of glucose 10% will be stopped and switched again to glucose 5%.

Early PN", this nutritional regime is the standard therapy in the participating centres and therefore accounts as the "control-group".

All centres will use their current pharmaceutical nutritional products for enteral as well as parenteral nutrition. The differences between the products provided by the different pharmaceutical companies are small clinically irrelevant differences in glucose, lipid and protein intakes.

Despite the different pharmaceutical companies, nutritional regimes from all participating centres will be aiming for the same energy and protein targets.

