#### 18.1.2 Secondary study parameters/endpoints

##### Work Package 1

All analyses will be performed uncorrected as well as corrected for age, nutritional status and risk categories and type and severity of illness. Time-to-event analysis will be analyzed similarly as the primary endpoint. Proportion of patients requiring support of vital organ functions and distribution of duration of support will be analyzed by non-parametric or parametric testing depending on the normality of the distribution in the subgroup of patients for which support was needed. Proportions will be compared using chi-square testing. Results of repeated measurements will be analyzed using an appropriate model for longitudinal data.

a. Time to final (alive) weaning from mechanical respiratory support: patients still on

mechanical respiratory support at closing of the data file (90 days after last patient

inclusion) will be censored at that time point. ICU non-survivors will be censored

beyond the longest duration of mechanical respiratory support of the survivors.

b. Kidney failure: Proportion of patients in need for renal replacement therapy (RRT)

during ICU stay; distribution of duration of RRT (for those patients requiring RRT);

proportion of patients with a post-randomization diagnosis of new kidney injury/failure

(defined by modified Risk, Injury, Failure, Loss, and End-stage Kidney (RIFLE)

classification criteria as a plasma creatinine doubling or more during ICU stay) in both treatment groups. In addition, the duration of a score RIFLE $\geq$ 2 will be used as a marker of time to recovery of kidney damage.

c. Need for pharmacological or mechanical haemodynamic support during ICU stay, and duration of such need.

In addition, time to final (alive) weaning from all pharmacological or mechanical haemodynamic support in ICU will be analyzed, with ICU non-survivors censored beyond the longest duration of pharmacological or mechanical haemodynamic support of the survivors and censoring time of patients still on such support at closing of the data file (90 days after last patient inclusion) over both treatment groups.

d. Number of readmissions to the PICU.

e. Liver dysfunction: Proportion of patients during the time window of the intervention and during the whole ICU stay presenting with cholestatic or cytolytic liver dysfunction will be compared.

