### **18.1.3 Other study parameters**

#### ***Safety endpoints***

Safety endpoints comprise vital status, hypoglycemia, SAEs and complications related to the mode of nutrition. Survival up to 90 days after randomization in both treatment groups will be compared by Kaplan Meier survival plots. The impact of “late PN” versus “early PN” will be analyzed, with and without correction for risk factors, by Cox proportional hazard analysis. In addition, we will record in-ICU and in-hospital mortality, and will analyze differences with Chi-square testing. As the randomized study intervention only takes place during a time window up to the 8th day in ICU, we also plan to analyze early lethality within this time window in the intention-to-treat population as part of the safety analysis.

As patients not receiving early PN may be considered at increased risk for hypoglycemia, we will report for both groups the number of patients experiencing hypoglycemia <40 mg/dl during the time window of the randomized intervention. Hypoglycemia resistant to parenteral glucose administration is considered as a SAE and the incidence during the time window of the randomized intervention will be reported for both groups. In addition, overall blood glucose control during the time window of the intervention will be compared using daily morning blood glucose as well as daily maximal and minimal blood glucose.

Safety issues also comprise the occurrence of feeding-mode-related complications during the time window of the intervention. Therefore, occurrence of these complications (digestive intolerance, complicated insertion of feeding tubes, pneumothorax, haemothorax and subclavian or carotid artery puncture, occlusion or displacement of central venous catheters or gastric feeding tubes) will be reported for both treatment groups.

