#### ***Outcome characteristics***

All medications received by the patients during ICU stay are registered. Every day the amount of kilocalories, lipids, proteins, carbohydrates delivered by either PN or EN are calculated from the PDMS in an automated manner and entered into the case record form (CRF). Interruptions of EN delivery and predefined digestive intolerance are registered daily. Mechanical complications such as displacement or obstruction of the enteral feeding tube or the central venous catheter, and clinical complications such as pneumothorax, hemothorax and subclavian or carotid artery puncture are recorded daily. All medications received by the patients during ICU stay are registered. Every day the amount of kilocalories, lipids, proteins, carbohydrates delivered by either PN or EN are calculated from the PDMS in an automated manner and entered into the case record form (CRF). Of the gastric residual volume discarded, half of the volume will be considered to be EN and half gastric secretions. The duration (in min) and cause of interruption of delivery of EN will be recorded. Digestive

intolerance will be registered as vomiting, tracheal aspiration of enteral feeding (defined 8), diarrhea, and gastric residue above 5ml/kg (see appendix for definitions). Tube displacement or obstruction will be labeled as mechanical complications. Occlusion and dislodging of central venous catheters will be recorded as mechanical complications. Pneumothorax, hemothorax and arterial puncture will be recorded as clinical complications. Number of ICU days with a central line in situ will be noted. The characteristics will be monitored until discharge from ICU, day 90 of hospital stay or death.

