## 19. SAFETY REPORTING

The risk in participating to the study and being randomized to the "late PN" group are negligible, and specifically compass an increased risk of developing hypoglycemia and/or underfeeding. However, safety measures will be taken to further decrease these risks. Our study may provide support for current practice, may give "neutral" results for which the cost-effectiveness study will provide necessary information for guiding therapy, or may challenge the presumed innocence of PN. Thus, there is no risk associated with the intrinsic value of these results.

The burden is expected to be minimal as it will only entail additional blood draws, which will be taken from clinical lines or in addition to pricks for clinical purpose. The long-term follow up will be held as part of already organised follow-up outdoor clinics and which are developed to help children and their parents to recover physically, emotionally and socially after ICU admissions. For mechanistic and exploratory studies, muscle strength testing and an ultrasound evaluation of the skeletal muscle and adipose tissue compartments will be performed. Furthermore, as far as practically feasible, every patient is approached just prior to hospital discharge, to complete a validated, semi-structured child health questionnaire (Functional Independence Measure (WEEFIM), Health Utilities Index (HUI) and Child Health Questionnaire (CHQ)).

In order to monitor the quality of the enteral and parenteral nutrition management during the study we will register all known complications possibly related to them. These complications should not be considered as adverse events since the study intervention is to withhold parenteral feeding during one week. These known complications of parenteral feeding will not be reported to the sponsor until the end of the trial.

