#### *Outcomes*

Primary outcomes are incidence of new infections and duration of PICU dependency, which will be reported as the crude number of PICU days and as the time to live discharge from the PICU, to account for mortality as a competing risk.

Secondary outcomes are duration of mechanical ventilation (and time to life weaning from mechanical ventilation), duration of hospital stay (and time to life discharge from the hospital), and the safety outcomes 7-day mortality (i.e. during the intervention period), 90-day mortality and hypoglycemia during the first week.

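### Line and catheter complications are compared only within the intervention window, although late-PN children with insufficient enteral feeding start PN on day 8

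*Supplement*

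**What the plan says.** Section 18.1.3 of the final protocol states the scope of the comparison: "Safety issues also comprise the occurrence of feeding-mode-related complications during the time window of the intervention". The list that follows covers digestive intolerance, feeding-tube problems, pneumothorax, haemothorax, arterial puncture, and occlusion or displacement of central venous catheters. Sections 19 and 19.2 repeat the same restriction.

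Four other places bear on it:

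- **Start of PN in the late arm (16.1).** If enteral feeding of at least 80% of calculated calories "is not possible after 7 days in ICU, PN, as specified below, is initiated on day 8".
- **Data collection (18.3, Outcome characteristics).** The same complications are recorded daily, and "The characteristics will be monitored until discharge from ICU, day 90 of hospital stay or death".
- **Adverse-event status (19).** "These complications should not be considered as adverse events since the study intervention is to withhold parenteral feeding during one week". The section adds that known PN complications go to the sponsor only at the end of the trial.
- **Liver dysfunction (18.1.2, item e).** Here the plan names two periods: "Proportion of patients during the time window of the intervention and during the whole ICU stay presenting with cholestatic or cytolytic liver dysfunction".

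The window is worded in two ways. Section 18.1.3 has the intervention running up to the eighth ICU day; the general rules in 20.1 speak of a 7-day window.

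**The concern.** The trial compares two strategies: PN early, or PN after a week if still needed. A complication of PN started on day 8 is an outcome of the late strategy. In the planned table, an early-arm arterial puncture on day 2 is counted, while one on day 9 in a late-arm child who has just begun PN is not.

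For harms attached to a procedure or to the start of PN, the table cannot separate harm prevented from harm moved outside the observation period. The error would favour late PN. It would concern the long-stay children, who are the only ones in that arm to receive study PN at all.

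**Working it through.** The plan states no figure on this point, so there is none to reproduce, and the sample size is unaffected. Two things can be estimated: how many late-arm children could start PN after the window, and how far the window could distort a difference between arms.

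**Inputs.** Section 15.1 gives 2010 ICU stays: Leuven median 3 days, interquartile range 2–6, mean 5.5; Rotterdam median 2, mean 7.8. Section 15.4 gives 720 children per arm. The lognormal shape is my assumption.

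**Step 1: share staying beyond day 7.** P(stay > 7) = 1 − Φ(ln(7/median)/σ). From quartiles, σ = ln(Q3/Q1)/(2 × 0.6745). From the mean, σ = √(2 ln(mean/median)).

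| Fit | σ | P(stay > 7 d) | × 720 |
|---|---|---|---|
| Leuven, quartiles | ln(3)/1.349 = 0.81 | 0.149 | 107 |
| Leuven, mean | √(2 ln(5.5/3)) = 1.10 | 0.221 | 159 |
| Rotterdam, mean | √(2 ln(7.8/2)) = 1.65 | 0.224 | 161 |

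The Leuven upper quartile of 6 days caps the Leuven share below 25% whatever the shape. The trial enrols children expected to stay more than 24 hours. Dropping stays of one day or less raises the three shares to about 16%, 26% and 34%.

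**Step 2: who then starts PN.** Only long-stayers still below the enteral threshold do, and the documents do not give that share. If it is 25% to 75%, the number runs from 0.25 × 107 ≈ 27 to 0.75 × 161 ≈ 121 late-arm children whose whole PN exposure falls after day 7. These are children exposed, not events.

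**Step 3: harm attached to each PN start.** Let each start carry a risk r, let every early-arm child start PN, let P be the share staying beyond day 7, and let q be the share of those who start PN in the late arm.

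- Difference in the window: r − 0 = r.
- Difference over the whole stay: r − rPq = r(1 − Pq).
- Share of the window difference that is only postponed: Pq, which is at most P when q = 1.

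That gives at most about 15–22%, or up to 34% with one-day stays dropped. If not every early-arm child starts PN, the window difference is smaller and the postponed share larger.

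**Step 4: harm accruing per PN-day.** Assume a constant daily risk and, after day 7, PN in a share of 50% or 100% of long-stayers in both arms. Dropping stays of one day or less and capping stays at 90 days, simulation gave these differences between arms, in percentage points:

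| Fit and daily risk | Window | Whole stay |
|---|---|---|
| Leuven, mean, 1% | 4.0 | 3.9–4.0 |
| Rotterdam, mean, 1% | 4.2 | 3.9–4.1 |
| Rotterdam, mean, 2% | 8.2 | 7.2–7.7 |

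After day 7 both arms accrue at the same rate, so the later events largely cancel. Here the window difference is close to the whole-stay difference, and the shorter exposure is real prevention.

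**The case against.** A reader might infer that all PN-related harm in the late arm escapes the safety comparison. The documents do not support that. New infections, with catheter-related bloodstream infection classified separately, are recorded over the entire ICU period up to day 90 (section 14). Liver dysfunction is compared over the window and the whole stay. ICU and hospital mortality and 90-day survival are compared. Serious adverse events in general carry no window. What is left is the mechanical and line-insertion group.

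A reader might also add hypoglycaemia, which the protocol confines to the window and the SAP to the first week ("90-day mortality and hypoglycemia during the first week"). That does not follow either. Section 18.1.3 gives the reason for tracking it: "As patients not receiving early PN may be considered at increased risk for hypoglycemia". It is a feared harm of withholding PN, and the window covers the period of withholding. The SAP covers a secondary analysis centred on undernourished children and lists no feeding complications, so it needs no change on this point.

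The cut-off also applies to both arms, so early-arm complications after the window go uncounted too. Step 4 shows that for risk per PN-day this leaves the contrast nearly intact. Digestive intolerance and feeding-tube events are complications of enteral feeding, so the postponement argument does not reach them.

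Nor is it certain that these events never reach adverse-event reporting. Section 19.2 says the safety endpoints it has just listed are handled in the standard timeframe, which sits poorly with the exclusion in section 19.

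All of this narrows the point. It does not remove it for procedure-linked harms, where no whole-stay report is planned and adverse-event reporting is at best an unclear route.

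**Conclusion.** The point stands for pneumothorax, haemothorax, arterial puncture and catheter occlusion or displacement, so far as these follow line placement or the start of PN. For them, the planned table can show a postponed event as absent in the late arm.

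The affected group is a minority: about 15–22% of children stay beyond day 7 under the lognormal assumption, roughly 107–161 of 720, and only some of these start PN. Under a risk per PN start, the postponed share of the window difference is at most about 15–34%, given that every early-arm child starts PN. Under a risk per PN-day it is small. The stay figures describe all 2010 admissions at two of the three centres, not trial patients, so these are orders of magnitude. They do not establish a general bias towards late PN. Which pattern occurred can be learned only from the whole-stay data.

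**What to change.** In 18.1.3, 19 and 19.2, add a report by arm of feeding-mode complications over the whole ICU stay (randomisation to ICU discharge, death or day 90). Place it beside the window report, as item e of 18.1.2 does for liver dysfunction. The two can stand in parallel; the whole-stay row need not become the main comparison. Because the trial expects ICU stay to differ by arm, also give ICU days or central-line days at risk, so that counts are not confused with exposure time. Section 18.3 already records days with a central line.

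Define the window once. The two wordings, up to the eighth ICU day in 18.1.3 and 7 days in 20.1, decide whether events on day 8 are counted and must be reconciled. State also whether the exclusion in section 19 or the handling in 19.2 governs these complications.

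The cost is a sentence in each safety section and one extra table row. No new data are needed. The small downside is that later events are less specific to the randomised window, which is why the window row stays.

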## **18.2 Randomisation, blinding and treatment allocation**

### ***Randomization***

The study will use a prospective, randomized, controlled, parallel-group design. On admission patients will be randomly assigned to receive EN combined with early PN or only EN. At ICU admission, consecutive patients will be randomly assigned to one of these two treatment groups using a centralized computer randomisation. Randomisation will be done in a 1:1 allocation ratio in permuted blocks of 10 (The block size remains unknown to bed-side physicians and nurses, responsible for patient recruitment and therapy assignment) and stratified according to primary diagnostic category on admission:

I Medical-ICU admissions (infectious or non-infectious): (a) respiratory (b) cardiac (c) renal (d) haematological/oncological (e) gastro-intestinal/hepatic (f) neurological (g) other.

II Surgical-ICU admissions (elective or urgent) according to referral discipline (a) cardiac surgery (b) solid organ transplants (c) pulmonary/oesophageal surgery (d) abdominal surgery (e) neurosurgery (f) trauma/orthopaedic surgery (g) burns (more than 20% BSA is burned and/or patient requires ventilation)

### ***Blinding of treatment allocation***

Treating physicians and patients cannot be blinded. All outcome assessors, which are investigators not directly involved in the patients care (such as statisticians, laboratory personnel, infectious disease specialists, pathologists and physiotherapists involved in the strength measurement) as well as physicians and nurses in the conventional wards are blinded to treatment allocation.

## **18.3 Study procedures**

### **Data collection following recruitment**

#### ***Baseline characteristics***

At baseline, data on demographic and clinical characteristics of the patients are obtained. Disease specific risk scores (such as the Risk-Adjustment in Congenital Heart Surgery or RACHS score) are calculated, co-morbidities and known use of important medications prior to admission are noted: these comprise, among others, the presence of congenital disease or syndrome, gestational age at birth, gender, ethnicity, paediatric risk scores, presence / history of cancer, diabetes mellitus, kidney failure, liver failure, chronic heart failure and sepsis upon admission. In addition, we record the need for and the number of days of mechanical ventilatory support, of mechanical and pharmacological haemodynamic support, of renal replacement therapies, days on antibiotics and days requiring a central line.

#### ***Outcome characteristics***

All medications received by the patients during ICU stay are registered. Every day the amount of kilocalories, lipids, proteins, carbohydrates delivered by either PN or EN are calculated from the PDMS in an automated manner and entered into the case record form (CRF). Interruptions of EN delivery and predefined digestive intolerance are registered daily. Mechanical complications such as displacement or obstruction of the enteral feeding tube or the central venous catheter, and clinical complications such as pneumothorax, hemothorax and subclavian or carotid artery puncture are recorded daily. All medications received by the patients during ICU stay are registered. Every day the amount of kilocalories, lipids, proteins, carbohydrates delivered by either PN or EN are calculated from the PDMS in an automated manner and entered into the case record form (CRF). Of the gastric residual volume discarded, half of the volume will be considered to be EN and half gastric secretions. The duration (in min) and cause of interruption of delivery of EN will be recorded. Digestive

intolerance will be registered as vomiting, tracheal aspiration of enteral feeding (defined 8), diarrhea, and gastric residue above 5ml/kg (see appendix for definitions). Tube displacement or obstruction will be labeled as mechanical complications. Occlusion and dislodging of central venous catheters will be recorded as mechanical complications. Pneumothorax, hemothorax and arterial puncture will be recorded as clinical complications. Number of ICU days with a central line in situ will be noted. The characteristics will be monitored until discharge from ICU, day 90 of hospital stay or death.

#### Blood samples

The maximum blood volume will be maximum 5 ml/kg for the entire study period. For a detailed description of the blood samples and tests see figure below. Blood samples are taken upon ICU admission and daily until discharge from ICU, or death. The blood samples will be taken from lines placed for clinical purposes or in combination with pricks requested for clinical purposes. A subset of the samples are immediately stored on ice for future endocrine measurements. Processed serum and plasma as well as the spun-down blood cells will be stored and frozen for mechanistic analyses.

All whole blood glucose levels are measured on arterial blood using a blood gas analyser on each ICU and are registered for later calculation of glucose metrics. Analyses on blood and urine for the primary clinical analyses include routine chemistry, haematology, and markers of inflammation. Further epigenetic, metabolic, endocrine and inflammatory measurements on stored samples in the context of mechanistic analyses will be stored until final analysis. Urine samples will be stored and frozen until final analysis.

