#### *Figure Samples.*

*Blood samples are taken upon ICU admission and daily at 06:00h until discharge from ICU, death or end of study. Upon admission three blood samples will be taken; namely two yellow "STOL"-tubes each containing a maximum of 3.5 milliliter blood and 1 purple "EDTA"-tube of 1.8 milliliter blood.*

*During the following days until the patient has left the PICU we will daily take a yellow "STOL"-tube (containing max 3,5 milliliter blood) and a purple "EDTA"-tube (containing 1,8 milliliter blood) for further analyses. On day 3,5 and 7 a 'PAX-tube' (containing 2 milliliter blood) will be collected. In children > 10 kg 1,8 milliliter extra blood (EDTA and heparine) will be collected on 4 selected days.*

*A subset of the samples will be immediately stored on ice for future endocrine measurements. Processed serum and plasma as well as the spun-down blood cells will be frozen and stored.*

*Analyses on the morning sample will include routine clinical chemistry, hematology (Hgb, WBC, TC), and markers of inflammation (CRP), liver function ALT, AST, ALP, GGT, bilirubin total/direct. A number of metabolic, hormonal and inflammatory study analyses will be performed on selected days.*

*The latter comprise, among others, coagulation & fibrinolysis tests, cytokines and markers of oxidative stress.*

*Also on selected days stool (single sample,) urine (5 tubes of 5 mL out of 24 hours' urine collection), 100 strands of hair and buccal swabs will be stored for further evaluation.*

*All whole blood glucose levels are measured on arterial blood using a blood gas analyser on each ICU and are registered for later calculation of glucose metrics.*

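### If the scheduled tubes count as study blood, the readable tube schedule cannot be completed within the 5 ml/kg cap in small infants who stay about a week, and the readable text does not say which rule gives way

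*Supplement*

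**What the plan says.** The Blood samples paragraph of section 18.3 (final protocol) gives the limit, "The maximum blood volume will be maximum 5 ml/kg for the entire study period", and then points on: "For a detailed description of the blood samples and tests see figure below". Sampling is on admission and daily until ICU discharge or death, with no stop at day 7.

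The readable text under Figure Samples is itself a tube schedule:

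- **Admission:** two STOL tubes and one 1.8 ml EDTA tube ("tubes each containing a maximum of 3.5 milliliter blood and 1 purple").
- **Later days:** "During the following days until the patient has left the PICU we will daily take a yellow" STOL tube of at most 3.5 ml, plus one EDTA tube of 1.8 ml.
- **PAX:** "On day 3,5 and 7 a 'PAX-tube' (containing 2 milliliter blood) will be collected".
- **Larger children:** "In children > 10 kg 1,8 milliliter extra blood (EDTA and heparine) will be collected on 4 selected days".

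The last item is the only one tied to body weight. The EDTA and PAX volumes are stated as plain figures; only the STOL volumes are worded as maxima. The same text says that the morning sample also serves routine chemistry, haematology, CRP and liver tests.

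Section 15.1 describes the population as 0 to 18 years. Section 15.3 excludes newborns born before 37 weeks and sets no minimum weight.

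**The concern.** The cap is a safety limit for children, and the schedule is what bedside staff would follow. For a small infant who stays a week, carrying out the schedule as written takes more blood than the cap allows, if the tubes count towards it. The readable text does not say that the cap overrides the schedule, which tube to omit, who keeps the total, or whether the limit covers study blood only.

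Which tube gives way also matters for secondary outcomes. Liver dysfunction and the daily CRP profiles (18.1.2, items e and f) rest on the morning sample, whereas PAX and the stored tubes serve mechanistic work. Without a stated order, either kind may be lost.

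**Working it through.** The plan gives no total tube volume and no minimum weight, so there is no figure of its own to reproduce.

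**Inputs.** Cap 5 ml/kg (Blood samples). EDTA 1.8 ml per day, PAX 2 ml on days 3, 5 and 7, STOL at most 3.5 ml, two on admission and one per later day (Figure Samples). Admission is day 1 (Additional data collection, buccal swabs). Body weights are assumptions, because the documents give no weight distribution.

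**Formulas.** By day D:

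- EDTA + PAX = 1.8 × D + 2 × (number of days 3, 5, 7 reached)
- full STOL adds 3.5 × (D + 1)
- weight needed = volume / 5

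| Day | EDTA + PAX, ml (kg needed) | with full STOL, ml (kg needed) |
|---|---|---|
| 3 | 7.4 (1.48) | 21.4 (4.28) |
| 5 | 13.0 (2.60) | 34.0 (6.80) |
| 6 | 14.8 (2.96) | 39.3 (7.86) |
| 7 | 18.6 (3.72) | 46.6 (9.32) |
| 8 | 20.4 (4.08) | 51.9 (10.38) |

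Day 7 in full: 7 × 1.8 + 3 × 2 = 12.6 + 6.0 = 18.6 ml, and 18.6 / 5 = 3.72 kg. Full STOL adds 8 × 3.5 = 28.0 ml, giving 46.6 ml, and 46.6 / 5 = 9.32 kg.

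**Which blood counts (day 7).**

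| Counted towards the cap | ml | kg needed |
|---|---|---|
| PAX only (all morning tubes clinical) | 6.0 | 1.2 |
| EDTA only | 12.6 | 2.52 |
| EDTA + PAX, STOL as zero | 18.6 | 3.72 |
| plus half-filled STOL (8 × 1.75 = 14.0) | 32.6 | 6.52 |
| all tubes full | 46.6 | 9.32 |

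**First day over the cap, at assumed weights.**

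| Weight | Cap, ml | EDTA + PAX | All tubes full |
|---|---|---|---|
| 3 kg | 15 | day 7 | day 3 |
| 4 kg | 20 | day 8 | day 3 |
| 5 kg | 25 | day 11 | day 4 |
| 10 kg | 50 | day 25 | day 8 |

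**Day convention.** If admission were day 0, EDTA + PAX would be 8 × 1.8 + 6 = 20.4 ml (4.08 kg). The convention used here is the lenient one.

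**How many children.** Section 15.1 gives a Leuven inter-quartile stay of 2 to 6 days, for all 2010 admissions and not by weight. On that figure a stay of seven days or more concerns roughly the longest-staying quarter or fewer. Enrolled children, who must be expected to stay more than 24 hours, may differ.

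**The case against.** **The cap governs.** The limit comes first in the paragraph and is worded as an absolute, so the tube list can be read as nominal. This is probably what was meant. A reader might infer from the sums that infants would be overdrawn; the documents do not support that, since staff may well have stopped at the cap. What stands is that two stated rules disagree and no readable sentence ranks them.

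**The figure is not shown.** The Blood samples paragraph refers to it for detail, and a weight table there cannot be excluded. The text printed with it, however, already sets the daily volumes, and its only weight rule is the one above 10 kg.

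**The morning tubes are clinical blood.** They feed routine tests, and draws are taken from existing lines or together with clinical pricks. If all of them are clinical, 6.0 ml of PAX remains and the conflict disappears at term weights. Against this, the daily EDTA tube is described as "containing 1,8 milliliter blood) for further analyses", and the protocol Summary counts extra blood draws as the burden of taking part. The text is ambiguous, so 3.7 kg is a conditional figure.

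**Little follows for the results.** This is right. A reader might infer harm to the trial's comparison, but new infections and time to live discharge do not depend on these tubes. The SAP's outcomes include no CRP or liver measure.

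**Conclusion.** The point holds in conditional form. If the scheduled tubes count as study blood, the readable schedule and the 5 ml/kg cap cannot both be met in small infants who stay about a week. The threshold at day 7 is about 3.7 kg on EDTA and PAX alone, which gives the STOL tubes no volume at all, and up to about 9.3 kg with every tube full. If all morning tubes are clinical, there is no conflict at term weights.

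The arithmetic is exact. The uncertainty lies in which blood counts and in the unseen figure, so confidence is medium. This is a safety and feasibility matter in a limited group, and it should be fixed because it touches the protocol's own limit for children. It is neither evidence that the cap was exceeded nor a threat to the primary endpoints, the SAP outcomes or the treatment comparison.

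**What to change.** Add to the Figure Samples text:

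1. The 5 ml/kg cap prevails over the schedule, and it counts blood drawn for the study beyond clinical need.
2. A running total is kept for each child, at every weight, and no study tube is taken that would pass the cap. (At 10 kg, full tubes reach 51.9 ml against 50 ml on day 8.)
3. PAX tubes are collected only if the child's remaining allowance permits.
4. Drop order: PAX first; then other stored mechanistic tubes; last the morning-sample blood for CRP, liver tests and haematology, which should come from the clinical sample where possible.

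The second step of that order is needed. At 3 kg, with every tube counted, dropping PAX leaves 15 − 12.6 = 2.4 ml for eight STOL tubes by day 7. Fixed weight bands or fill volumes are not needed: they would remove samples from children whose allowance still covers them, and the documents give no minimum laboratory volume on which to base a fill.

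The cost is a few sentences, one running-total field and fewer mechanistic samples in the smallest and longest-staying children. Some daily CRP, liver or haematology values may also be missing once the cap is reached and no clinical sample exists.
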